
Recently, several authors have undertaken studies to identify biomarkers linked to FM by analyzing plasma proteomic profiles using advanced proteomic techniques. Ramírez-Tejero et al. (14) identified 33 proteins exhibiting differential expression in FM patients compared to controls, with a majority of proteins associated with inflammatory processes. Another study (15) revealed differences in proteins involved in inflammatory, metabolic, and immune processes, demonstrating a correlation between these proteins, patients’ pain perception and psychological distress. Han et al. (16) discovered 22 differentially expressed proteins in FM patients compared to pain-free controls primarily associated with blood coagulation processes, immune response and interactions with extracellular matrix receptors. Collectively, these findings highlight the role of coagulation, inflammation and immune response in the pathogenesis of the disease.

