
The dietary habits of individuals play a key role in influencing the gut microbial community and its metabolic activities. Among healthy dietary choices, Mediterranean-style diets stand out, as they are associated with the prevention of various diseases, including cardiovascular and metabolic disorders, colorectal cancers and other chronic and acute processes (26). The positive effects of such diets are likely due to their high content of fibers, mono-and polyunsaturated fatty acids, antioxidants and polyphenols (26). Research has shown that adopting a Mediterranean-style diet leads to improvements in serum inflammation biomarkers and gene expression profiles (nutrigenomics) (27). Olive oil is an essential element in the Mediterranean diet and is known for its beneficial properties. Olive oil polyphenols possess a range of health benefits, including antioxidant, anti-inflammatory, antimicrobial, antiviral, anti-atherogenic, anti-thrombotic, anti-mutagenic and hypoglycemic characteristics. With regard to oxidative stress, consumption of high-phenol olive oil can help reduce cellular oxidative damage. Furthermore, it has the potential to lower the concentration of inflammatory markers and to enhance antioxidant capacity (28). Testing of this nutritional intervention as a therapeutic treatment in FM patients has shown that beneficial results are obtained in relation to oxidative DNA damage and antioxidant levels (29). These results could be explained by the close relationship between nutrient absorption and an adequate mitochondrial function.

In summary, FM is a chronic and complex condition that is highly underdiagnosed due to the lack of reliable biomarkers that might facilitate accurate diagnosis and disease monitoring. Hence, the primary focus of this study is to develop a targeted panel of specific plasma and fecal biomarkers capable of diagnosing this condition from readily obtained biological samples. Furthermore, the secondary objective is to investigate how nutrition can influence the modulation of these biomarkers. Identification of accurate biomarkers through this study is the key to advancing our understanding and management of FM, ultimately leading to improved patient outcomes.

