#### Plasma proteome analysis

2.4.2

Whole blood samples from participants will be collected through venipuncture performed by a healthcare professional. The samples will be collected in two tubes containing heparin-lithium as an anticoagulant. Moreover, to minimize circadian fluctuations of the markers, the blood samples will be taken at the same time of day and participants will have fasted beforehand. While one of the tubes will be used for oxidative stress and mitochondrial metabolism analysis, the other one will be transferred to a 15 ml Falcon tube and then centrifuged at 2,300 RCF for 10 min at 4°C. This process will isolate the plasma, the sample to be used in the proteome analysis that will be aliquoted and stored at −80°C until batch analysis (maximum storing: 5 months). To analyze the plasma proteome, liquid nano-chromatography coupled to the tandem mass spectrometry (nLC-MS/MS) proteomic method will be applied. This analysis will utilize the EvoSEP chromatograph,^1^ which is one of the highest resolution and processing chromatographs available. It is a unique instrument in Spain and is accessible through the services of the BioGUNE Cooperative Research Center in Biosciences located in Biscay, Spain. The processed data will be analyzed with the search engines MASCOT (MatrixScience) and/or PEAKS (Bioinformatics Solutions Inc). Label-free quantification differential proteomics will be performed using PEAKS (Bioinformatics Solutions Inc) and/or MaxQuant software. Quality control of samples will be applied at each step through protein-suitable techniques such as Bradford quantification, electrophoresis and/or Ponceau staining.

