#### Microbiota and intestinal permeability analysis

2.4.5

Participants will collect fecal samples using the DANASTOOL sample collection kit (Danagen; Barcelona, Spain). They will use a Fe-Col^®^ Faecal sample collection paper (Alpha Laboratories; Hampshire, United Kingdom) as a stool-catch platform. The participants will scoop a small portion of stool into the provided stool tube, which contains a liquid DNA/RNA stabilization solution. Following collection, all samples will be stored in accordance with established quality standards. Since the DANASTOOL sample collection kit has a DNA/RNA stabilization solution, samples were stored at room temperature until batch analysis. DNA extraction from fecal samples will be carried out using the DANAGENE MICROBIOME FECAL DNA KIT (Danagen; Barcelona, Spain). Briefly, 1 ml of homogenized sample was transferred to a tube containing beads to ease sample disruption. Then, samples were incubated at 70°C during 10 min. After incubation step, a thorough vortexing and centrifugation steps were applied. The upper phase was then transferred to a filtering column to extract DNA by centrifugation. The extracted DNA will then be used to analyze the composition of the gut microbiota. This analysis will involve amplicon metagenomics sequencing, in which amplicons of V3–V4 regions from the 16S rDNA will be sequenced using the Illumina MiSeq platform at HelixBioS (Madrid, Spain) facilities. A tagging and barcoding process suitable for Illumina technology will be conducted, according to manufacturer instruction. Each sample will undergo individual quantification, pooling, washing and titration using qPCR. The sequencing will be performed on the MiSeq platform with a fragment size ranging from 2 × 250 to 2 × 300, with the aim of generating 150,000 to 200,000 reads per sample. We will set the minimal number of reads per sample at 50,000 as quantity threshold, and Phred Score at Q30 as quality threshold. Samples with an average trimmed read length below 280 bp will be discarded. All these quality control procedures will be applied through MultiQC software (36) and sequencing results will be analyzed with USEARCH V11.1. Briefly, the reads will be cleaned using the UCHIME algorithm to eliminate “singletons” sequences (those that only had one copy in the total sequences), chimera sequences and possible artifacts. ZOTUs clustering will be carried out using the UNOISE algorithm at 99% identity (similarity). The sequences will be then aligned against the taxonomic database developed for the study of the intestinal microbiota, HUMAN GUT 16S (HelixBioS), with an alignment cut-off point of 99% (identity) using the algorithm USE-LOCAL. The results will be finally processed with phyloseq (37) and DESeq2 (38).

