
#### Statistical analysis

2.4.6

The statistical analysis will be performed in RStudio, using R v3.6.2 base packages. First, data distribution will be assessed by using the Kolmogorov–Smirnov test, which evaluates the null hypothesis that data correspond to normal distribution. In that case, in analyses of CONTROL vs. FM groups T_0_, parametric tests such as the unpaired student’s *t*-test and the Pearson correlation test will be used to investigate mean differences and correlation between quantitative variables, respectively. If data do not display normal distribution, the Mann–Whitney *U* test and the Spearman correlation non-parametric test will be applied for this purpose. Additionally, for comparison among groups when depicting nutritional intervention influence with treatment vs. placebo, pre-post analysis through analysis of covariance (ANCOVA) with multiple comparison correction will be used, since it has been shown to be the most powerful analysis for this experimental design (39). In all cases, the significance level (*α*) will be established at 0.05 so that null-hypothesis will be rejected when the *p*-value is <0.05. Tables will be used as preferred format to show descriptive data, such as demographic characteristics, stacked bar charts and/or pie charts will be used to represent distributions, bar charts and/or box and whiskers plots will be applied when showing differences in mean among groups and, finally, violin plots, volcano plots and additional statistical representations will be the format to show distribution and significance in the values found in each group.

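### Multiplicity correction is stated only for the diet ANCOVA, so the primary T0 FM-vs-CONTROL biomarker comparisons and the biomarker-score correlations have none as written

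*Protocol article*

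**What the plan says.** The Introduction states the aim: "the primary focus of this study is to develop a targeted panel of specific plasma and fecal biomarkers". The influence of nutrition on those markers is named there as the secondary objective.

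The Statistical analysis section (2.4.6) then makes three statements that bear on multiplicity:

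- For the primary question, it specifies that "in analyses of CONTROL vs. FM groups T_0_, parametric tests such as the unpaired student’s" t-test and Pearson correlation are used if the data look normal, with Mann–Whitney and Spearman otherwise. No correction is mentioned.
- For the diet question, "pre-post analysis through analysis of covariance (ANCOVA) with multiple comparison correction will be used".
- For all analyses, alpha "will be established at 0.05 so that null-hypothesis will be rejected when the" p-value is below 0.05.

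The platforms feeding the primary question are high-dimensional. In Plasma proteome analysis (2.4.2), "Label-free quantification differential proteomics will be performed using PEAKS" and/or MaxQuant. In Microbiota and intestinal permeability analysis (2.4.5), 16S sequence variants go through phyloseq and DESeq2. Neither section gives the number of features expected or says whether results are read on adjusted or unadjusted p-values. Health questionnaires (2.4.1) adds correlations between the scores and the biomarkers found.

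**The concern.** The section does deal with multiplicity, but places the correction on the secondary question and leaves the primary one without it. It then fixes a single rejection rule for everything. An analyst who follows the text would test each T0 feature, and each feature-score correlation, at 5%.

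The T0 comparison is a screen over many proteins and taxa. Without control, the expected number of false findings grows in proportion to the number of features, and a list of declared markers can contain a large share of noise. If the diagnostic panel is chosen from that list, the noise goes into the panel and into the correlations with symptom scores.

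**Working it through.** **Figures in the plan.** The plan gives no number of features, tests or expected false positives, so there is no multiplicity figure to reproduce. Its only computed figure, the minimum of 206 participants in section 2.2.1, comes from a prevalence-precision formula: 1.96² × 0.075 × 0.925 / 0.0375² = 189.5, and 189.5 × 1.1 = 208.5, close to 206. That formula contains no hypothesis test, so it says nothing about error rates in the screen.

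**Inputs.**

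- Alpha of 0.05: section 2.4.6.
- Group sizes: 250 recruited (section 2.2.2), in blocks of 4 patients and 4 healthy volunteers (section 2.1), hence about 125 vs 125.
- Assumed, not in the documents: the number of features m, the share truly shifted, and a shift of 0.5 SD.

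**Step 1: expected false positives if the rule is applied unadjusted.** The expectation is 0.05 × m for m null features. It does not require independence; the ranges do.

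| Null features (assumed) | Expected false positives | 95% range, independent features |
|---|---|---|
| 100 | 5 | 1 to 10 |
| 200 | 10 | 4 to 16 |
| 300 | 15 | 8 to 23 |
| 500 | 25 | 16 to 35 |
| 1,000 | 50 | 37 to 64 |

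The chance of at least one false positive among 100 independent null features is 1 − 0.95^100 = 99.4%.

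**Step 2: false share of the declared list.** Power for a 0.5 SD shift with 125 vs 125 at two-sided 0.05 is Φ(0.5 × √(125/2) − 1.96) = Φ(1.99) = 0.977. For 500 features:

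| Truly shifted | False hits | True hits | False share |
|---|---|---|---|
| 5% (25) | 475 × 0.05 = 23.75 | 25 × 0.977 = 24.4 | 49% |
| 10% (50) | 450 × 0.05 = 22.5 | 50 × 0.977 = 48.8 | 32% |
| 20% (100) | 400 × 0.05 = 20 | 100 × 0.977 = 97.7 | 17% |

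Both columns of hits scale with m, so the false share does not depend on the assumed number of features. It does depend on the share truly shifted and on the size of the shift.

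**Step 3: effect of a correction.** In a simulation of the 500-feature, 5% case (300 replicates, independent features), the unadjusted rule gave 24.4 true and 24.0 false hits. Benjamini-Hochberg at 5% gave 20.1 true and 1.1 false. Bonferroni at 0.05/500 = 0.0001 has power 0.525 for the same shift, or about 25 × 0.525 = 13 true hits. False discovery rate control therefore removes nearly all the false hits and keeps more of the true ones than a family-wise correction.

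**The case against.** The strongest reply is that the text never calls its p-values unadjusted. The rejection rule also covers the ANCOVA, where the p-value compared with 0.05 is a corrected one, so the rule fixes alpha and does not by itself exclude adjustment elsewhere. The 16S data go through DESeq2 and the proteome through PEAKS and/or MaxQuant, and section 2.4.6 does not say that its t or Mann–Whitney tests are the per-feature tests on either platform. A condensed article may also leave the procedure and the family to a fuller plan, and the Discussion places clinical use after further research.

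Much of this stands, and it limits what can be claimed:

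- A reader might infer that every test is read at a raw 5%. The documents do not support that: the ANCOVA is corrected, and how the software output will be read is not stated.
- A reader might infer that the screen will return dozens of false biomarkers. No feature count is given. An expectation of 24 needs 24/0.05 = 480 null features, all tested unadjusted; at 100 to 300 the expectation is 5 to 15. With 300 independent null features the chance of 24 or more is 1.7%.
- A reader might set these counts beside the earlier study that "identified 33 proteins exhibiting differential expression in FM patients compared to controls". The article gives neither the number tested nor the correction used there, so the comparison shows little.
- No section says that the panel is chosen by T0 significance alone. That link is an inference.

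What does not stand is the view that this is only detail left for later. The section states where correction applies, omits it from the primary comparison, and fixes the rejection threshold for all analyses. Nothing in the proteome or microbiota sections gives an adjusted threshold that would replace that rule.

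**Conclusion.** The point holds in this form: as written, the T0 FM-vs-CONTROL comparisons and the biomarker-score correlations have no multiplicity control, although they serve the primary aim, while the secondary diet analysis has it. If the 0.05 rule is applied unadjusted, about 5 false positives are expected per 100 null features. The false share of the declared list runs from about 17% to 49% as the truly shifted share falls from 20% to 5%.

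The absence of a stated correction rests on the text alone. The sizes rest on assumed feature counts, an assumed 0.5 SD shift, 125 per group, and p-values read unadjusted. They show what the rule permits and do not predict this trial's results.

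**What to change.** Amend section 2.4.6 to state that:

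- T0 FM-vs-CONTROL feature tests and biomarker-score correlations are controlled by Benjamini-Hochberg at a 5% false discovery rate, within each platform (proteome; taxa);
- results from DESeq2 and from the proteomics software are read on adjusted p-values;
- for these families the 0.05 threshold applies to adjusted p-values.

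Holm across the few targeted markers (Q1, Q2 and QT of the antioxidant measure, VDAC, MAP1LC3B) is an optional addition.

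The change takes a sentence or two of text and one line of code, and alters nothing in recruitment or sampling. The price is some sensitivity: in the 500-feature example with 5% truly shifted, about 4 of 24 true hits are lost (24.4 − 20.1 = 4.3), while false hits fall from about 24 to about 1.

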## Discussion

3

FM is a chronic condition that is characterized by pain and for which there is still no precise molecular diagnosis in the healthcare community. Therefore, the main objective of FIBROKIT is to develop a panel of specific biomarkers that can facilitate precise diagnosis and monitoring of the disease. This research will enhance our understanding of the role of oxidative stress, mitochondrial metabolism, intestinal microbiota and inflammation in the pathophysiology of FM. This study introduces a novel approach by designing a comprehensive panel of specific biomarkers for the disease which has not been previously documented. Furthermore, the inclusion of 250 patients represents a significantly larger sample size compared to similar studies, which will help to find relevant results with a strong statistical significance and power. The main goal and greatest challenge of FIBROKIT is the transfer from omics platforms to a group of proteins and microorganisms to be measured by an easy and reproducible wet-lab technique.

Previous studies conducted by this research group have demonstrated an increase in oxidative stress and the presence of mitochondrial dysfunction in FM (40). Furthermore, several studies (10, 41) have reported an increase in the TAC among FM patients, indicating a higher level of oxidative stress in this population. In this context, it is expected that FIBROKIT will find mitochondrial and oxidative markers among its candidates for biomarker discovery. Organelles as well as macromolecules have been widely studied in FM patients. Thus, studies conducted by Ramírez-Tejero et al. (14) and Wåhlén et al. (15) have emphasized the involvement of proteins associated with blood coagulation, immune response and extracellular matrix-receptor interactions, highlighting the role of these pathways in the pathophysiology of the disease and, at the same time, reinforcing the role of proteins as powerful biomarkers in FM. All these responses have been frequently linked to FM, being related with pain, joint stiffness, low-grade chronic inflammation and a severe fatigue (14). Consequently, proteins related with these pathways will serve, not only for diagnostic, but also for personalized treatment for FM patients. In this sense, FIBROKIT will likely involve plasma proteins linked to these pathways, closely related to the main FM symptoms such as pain and fatigue. Focusing on the intestinal microbiota hypothesis, a study (25) has shown reduced bacterial diversity in FM patients, specifically a decrease in *Bifidobacterium* and *Eubacterium* genera. This study also showed disrupted levels of glutamate and serine in FM patients, indicating potential alterations in neurotransmitter metabolism. However, the study conducted by Albayrak et al. (42) revealed significant changes in the patient group, with a statistically significant increase in *Bacteroidia* and *Bifidobacterium*, as well as a decrease in *Firmicutes*. Additionally, this study reported non-significant differences in the abundance of *Enterobacter*, *Streptococcus*, and *Lactobacillus*. A systematic review (43) indicated that the differences in microbiota were found to be associated with both the diagnosis and symptoms of FM. Notably, *Bacteroides* spp. exhibited a positive correlation with the FIQ total symptom score and 2016 ACR diagnostic criteria. Furthermore, there was an increased abundance of *Parabacteroides merdae*, and although not statistically significant, a trend of increased *Akkermansia muciniphila* was also observed. In addition, a separate study has shown that following the Khorasan wheat diet leads to improvements in various FM symptoms, accompanied by alterations in certain gut bacteria (44). This investigation reported positive correlations among *Actinobacteria*, *Verrucomicrobiae*, *Saccharibacteria*, *Bacteroidales* and specific questionnaire scores related to FM symptoms. These findings serve as a basis for the current study, which is expected to obtain results in accordance with those described.

The main study limitation is the marked sex bias. However, this is a predefined bias based on the preponderance of females among FM sufferers. Other study limitations are related to participants’ performance. For instance, self-questionnaires are widely used for nutritional follow-up and health assessment, but it is difficult to determine whether participants are being honest. Additionally, participants’ adherence to the nutritional intervention will be a significant obstacle, as a 1 year study requires significant commitment. Finally, as a multicenter study, coordination of logistical and clinical appointments is presumably a difficult task, and special attention will be required over the course of the project.

In summary, FIBROKIT will be the first study in FM patients to enroll more than 200 patients for biomarker discovery research. At the end of the project, it will be assessed whether plasma and feces may be considered suitable samples in which to look for a differential signature between FM patients and healthy controls. Furthermore, biomarkers’ identification will shed light on molecular diagnosis of FM, as well as will provide potential useful therapeutic targets to deepen in the field of personalized medicine for these patients. Whether theses biomarkers will be applied in clinical practice will need further research and clinical trials with drugs and non-pharmacological therapies.

## Ethics statement

This research, conducted with human participants, underwent a thorough review and received approval from the Ethical Committee for Research with Medications (CEIM) at the Quirónsalud-Catalunya Hospital Group. All participants provided written informed consent prior to their involvement in the study.
